**Data collection method and location including who will be responsible for the data collection**

Participation in this research project is voluntary. If one does not wish to take part, they do not have to. If participant decided to take part and later changed their mind, they are free to withdraw from the project at any time. If they decide to withdraw from the project after the data has been analysed, we will not be able to remove the individual data as this cannot be identified.

If participant do decide to take part, they will be given the participant information letter and consent form to sign, and they will be given a copy of the information letter to keep. They decision to take part, or to take part and later withdraw, will not affect they relationship with the research team and any staff within the School of Nursing and Midwifery at ECU.

By signing the consent form, they consent to the research team collecting and using personal information about the participant for the research project. Any information obtained in connection with this research project that can identify participant will remain confidential. When all survey responses are returned to the research team, all data are automatically de-identified, and they will not be identifiable by any of their responses to the survey. They information will only be used for the purpose of this research project and it will only be disclosed with they permission, except as required by law.

It is anticipated that the results of this research project will be published and/or presented in a variety of professional forums. In any publication and/or presentation, the information will be provided in such a way that participants cannot be identified, except where requested for specific reasons, and then they will be asked to provide written consent.

In accordance with relevant laws, participants have the right to request access to the information about them that is collected and stored by the research team. They also have the right to request that any information that they disagree to be corrected. They are encouraged to inform the research team member named at the end of this letter if they would like to access they information.

All data collected will be kept in accordance withData Management Policy. Electronic data will be stored on a secure Microsoft SharePoint site provisioned byBeijing LNKMED Tech Co., Ltd., Beijing, China, http://www.lnkmed.com/edc/a/sysIndex Services and physical records will be stored as required in Records Management Policy. The data will be retained for a period of seven years and destroyed, if appropriate at the end of the retention period. Data will be de-identified when stored and at the end of the retention period, the data will be destroyed, if appropriate under the State Records Act.

There are no foreseeable risks associated with participation in this research project.

We will advise participants of the outcomes via email communication. We also intend to publish our results in research journals and present them at research conferences locally, nationally and internationally. Participants' name or any other identifying information will not be included in any of the publications or presentations.

The Principal Investigator (PI) will log in to the EDC system, check the consistency of case report form and source data, and record the case report within the specified time. The researcher can answer the questions online or download the list of questions and answer offline. Then, the researcher input the questions into the EDC. The data administrator and supervisor can approve the researcher to answer questions and ask questions again if necessary.

The proposed randomized controlled trial was approved by the China Ethics Committee of Registering Clinical Trials (approval no: ChiCTR2100054234; http://www.chictr.org.cn/; version 2.0, as of December 9, 2021). This study is preparing for the patient recruitment stage.

**Statistical analysis**

For the primary outcome, rates of recruitment (numbers consented/eligible), completion (undertaken baseline and follow-up tests), adherence (participant completed sessions/number of sessions), and adverse events (number and number per participant hour) will be calculated. Secondary outcome will be assessed following intention-to-treat principles. Repeated measures ANOVA will be conducted to assess changes in secondary outcomes throughout the study. This model allows inclusion of missing data in an intention-to-treat analysis without imputations (e.g. last-observation-carried-forward). If necessary, analysis will be adjusted for baseline levels and potential confounding factors. Normality assumptions will be assessed using the Shapiro-Wilk test. Statistical significance will be set at an alpha level of 0.05. Corrections will be applied to all analysed outcomes to account for multiple comparisons.

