**Statistical analysis:**

Descriptive statistics

We will perform statistical analyses using SPSS statistical software (version 26.0, IBM Corp., Armonk, NY, USA). A mixed-effect model will be used to compare change values before and after treatment for continuous variables. This analysis model divides the baseline scores as study covariates, accounting for grouping and central effects. Based on this model and differences before and after treatment, we will calculate the least squares mean of the two groups and the associated 95% credible interval of the difference between the two groups. Fisher's exact parametric method and nonparametric Kruskal Wallis tests will be used to evaluate dichotomous variables. Report exact p-values for all values greater than or equal to 0.001.A two-sided P-value of < 0.05 is considered the threshold for statistical significance.

Metabolomics analysis

We will perform first signal denoising, baseline and phase correction for all spec graphs, piecewise data integration, row and column normalization, and scaling normalization to conduct the metabolomics analysis. All data are to be processed using MestReNova software (Mestrelab Research, Santiago de Compostela, Spain). Pattern recognition analysis includes adopting the principal component analysis method of unsupervised mode recognition as well as a classification analysis (SIMCA), a partial least squares method, and a neural network method. All of these procedures will be conducted using SIMCA-P software (version 14. 0, Umetrics AB, Umea, Sweden). Pearson correlation analysis will be used to analyze characteristic hematuria metabolites as well as to determine the metabolites specific to PDMM and their associated metabolic pathways.

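### The protocol gives two unreconciled analyses for the continuous secondary outcomes; the later one names no electroacupuncture-versus-sham contrast and makes baseline adjustment optional

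*Protocol*

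**What the plan says.** **First Statistical analysis section (sub-heading Descriptive statistics).** For continuous variables: "A mixed-effect model will be used to compare change values before and after treatment for continuous variables". On its terms: "This analysis model divides the baseline scores as study covariates, accounting for grouping and central effects". On the result to be reported: "we will calculate the least squares mean of the two groups", together with "the associated 95% credible interval of the difference between the two groups". Nothing limits this to the primary outcome, and baseline adjustment is not conditional. No visit or group-by-visit term is named.

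**Second Statistical analysis section (just before Risk).** For the secondary outcomes: "Secondary outcome will be assessed following intention-to-treat principles", and then "Repeated measures ANOVA will be conducted to assess changes in secondary outcomes throughout the study". Baseline is handled by discretion: "If necessary, analysis will be adjusted for baseline levels and potential confounding factors". The section also says that the model accommodates missing data without imputation, that "Statistical significance will be set at an alpha level of 0.05", and that all analysed outcomes will be corrected for multiple comparisons. It names no ANOVA term: not time, not group, not group-by-time.

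The secondary outcomes concerned are the 0–10 numerical pain scale, CMSS, the traditional Chinese medicine symptom score, the anxiety and depression self-rating scales and the SF-36.

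**The concern.** The trial is randomised and sham-controlled, so each secondary outcome should be judged on the difference between EA and sham. The first section states that target. The second describes its target as change over the study and mentions neither arm. Both are current text, and nothing says which one governs. An analysis plan could follow either and still claim to follow the protocol.

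The choice matters because improvement in both arms is plausible. Entry requires a VAS of at least 4 cm over three consecutive cycles, which invites regression to the mean in pain scores. Sham participants also receive shallow needling, the same electrode set-up and the same attention. A test of change over time would pick up that shared improvement and say nothing about EA. Separately, a baseline adjustment that is made only if thought necessary, with no rule for deciding, can be settled after both results are known.

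**Working it through.** **1. The two sections side by side**

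| | First section | Second section |
|---|---|---|
| Scope | continuous variables | secondary outcomes |
| Model | mixed-effect model of change | repeated-measures ANOVA |
| Baseline | covariate | only if necessary |
| Group, centre | both named | neither named |
| Reported result | difference between the two arms, with interval | changes throughout the study |

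The continuous secondary outcomes fall under both columns. The protocol states no error rate for either method, so there is no figure of its own to reproduce.

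**2. What follows if the time effect is tested and EA equals sham**

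Inputs: N = 336, or n = 168 per arm (Sample Size), and alpha 0.05. Assumed, because the protocol gives no values: SD σ = 2 points, within-person correlation ρ = 0.5 between all visits, T = 4 visits, and the same fall f in both arms at every visit after baseline.

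Noncentrality of the time F test: λ = N·Σ(μ_t − μ̄)² / [σ²(1 − ρ)], with Σ(μ_t − μ̄)² = f²(T − 1)/T = 0.75f². Degrees of freedom are T − 1 = 3 and (N − 2)(T − 1) = 1002.

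- f = 0: λ = 0, rejection 5%.
- f = 0.25: λ = 336 × 0.046875 / 2 = 7.875, rejection 64.5% (a simulation of the same case gives 66%).
- f = 0.5: λ = 336 × 0.1875 / 2 = 31.5, rejection 99.9%.

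The correction method is not named. With an illustrative 0.05/6 for the six scales, the last two become 38% and 99%.

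Range over other assumptions (simulation; baseline, week 12 and week 24; ρ from 0.3 to 0.7; alpha 0.05): the time test rejects 33–70% at a shared fall of 0.1 SD, 90–99.9% at 0.2 SD and at least 99.97% at 0.3 SD. In the same runs, group-by-time rejects 4.2–6.0% and the group main effect 4.2–5.6%, whatever the shared fall.

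**3. What follows if a group term is meant**

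Assume a true EA effect δ = 0.6 points (0.3 SD) from the first visit after baseline. For scale, 168 per arm detects (1.960 + 0.842) × √(2/168) = 0.306 SD with 80% power. Let d_t be the arm difference at visit t and d̄ its mean. For T = 4 and ρ = 0.5, d̄ = 0.45, Σ(d_t − d̄)² = 0.27 and 2/n = 0.0119.

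- Baseline-adjusted contrast at one visit: λ = δ² / [(2/n)σ²(1 − ρ²)] = 0.36 / (0.0119 × 3) = 10.08, power 89%.
- The same contrast unadjusted: λ = δ² / [(2/n)σ²] = 0.36 / (0.0119 × 4) = 7.56, power 78%.
- Group-by-time term: λ = N·Σ(d_t − d̄)² / [4σ²(1 − ρ)] = 336 × 0.27 / 8 = 11.34 on 3 and 1002 df, power about 82%.
- Group main effect, baseline included as a visit: λ = d̄² / [(2/n)σ²{1 + (T − 1)ρ}/T] = 0.2025 / (0.0119 × 2.5) = 6.80, power 74%.

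Over T = 2, 4 or 7 and ρ = 0.5 or 0.7, the adjusted contrast has 89–97% power, group-by-time 78–97% and the group main effect 32–88%. The unadjusted contrast stays at 78%. At ρ = 0.7 with 4 or 7 visits, group-by-time is about as good as the adjusted contrast.

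**The case against.** The strongest reply is that the second section never says the time effect is the test. It sits in a two-arm trial, the preceding sentence invokes intention-to-treat, and a two-arm repeated-measures ANOVA ordinarily carries group and group-by-time terms. Its remark on missing data also fits a mixed model better than a classical complete-case ANOVA. Naming the tested term is commonly left to the analysis plan, which is not shown.

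Much of this stands. A reader might infer that the plan tests a time-effect null and would therefore declare success almost regardless of EA. The documents do not support that: no term is named, and the high rejection rates need both that reading and a shared fall of roughly 0.2 SD or more. Nor can it be said that the protocol lacks an arm contrast for these outcomes, because the first section gives one for continuous variables.

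It would also go too far to say that all six scales would be declared improved. Selection is on VAS, so regression to the mean bears directly on pain measures. It does not carry over automatically to mood or quality of life, and a history of depression is an exclusion.

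What the reply does not remove is the conflict. Two methods and two rules on baseline apply to the same outcomes. That is a contradiction in current text, not a detail deferred to the analysis plan.

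**Conclusion.** The point holds as an unreconciled contradiction that should be resolved before analysis. The first section gives a baseline-adjusted difference between arms; the second gives a repeated-measures ANOVA of change with no stated arm contrast and discretionary adjustment.

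The size depends on how the second section is carried out. If change over time were tested, false claims of an EA effect would range from 5% with no shared fall to over 99% at 0.5 points. If a group or group-by-time term were tested, the error rate would stay near 5%, and the cost would be a usual, not universal, loss of power plus a choice left open after the data are seen. That last risk was not quantified. All figures rest on assumed SD, correlation, number of visits, shared fall and EA effect.

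**What to change.** In the second Statistical analysis section, delete the repeated-measures ANOVA sentence and the sentence on adjusting if necessary. State instead that:

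- every continuous secondary outcome is analysed with the mixed model of the first section, with group and centre as terms and the baseline score always a covariate;
- visit and group-by-visit are added, since the first section does not name them;
- the reported result is the EA-minus-sham least-squares mean difference with its 95% confidence interval (the first section says credible interval) at end of treatment and at end of follow-up;
- within-group or pooled changes over time are descriptive and carry no efficacy P-value.

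This changes wording only; no extra data or participants are needed. The price is that pooled before-after P-values can no longer support an efficacy claim. The edit does not settle a separate conflict in the same section, which treats recruitment, completion, adherence and adverse-event rates as the primary outcome while the Primary outcomes section describes VAS.

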**Secondary outcomes:**

Pain level on this scale is indicated by 11 numbers ranging from 0 to 10 (0 = painless, 10 = the most painful). The degree classification standard was scored as follows: 0 = painless, 1 to 3 = mild pain, 4 to 6 = moderate pain, 7 to 10 = severe pain. The participants will be scored according to their individual pain sensations. This method is easily understood by patients and can be either dictated or written. The CMSS is a total frequency score indicating an average severity evaluation of menstrual dysmenorrhea and includes information on specific symptoms of menstrual dysmenorrhea. Moreover, the traditional Chinese medicine symptom Score is formulated to score the evaluation of Chinese medicine symptoms according to the Guiding Principles for Clinical Research published by the Chinese Medical Science and Technology Press. The Self-Rating Anxiety Scale, Self-Rating Depression Scale, and 36-Item Short Form Survey are scales used to evaluate participants' mood and quality of life during treatment and follow-up. A metabolomics test on blood and urine samples is to be used to evaluate metabolic product changes occurring after the treatment of PDMM with EA and to provide findings informing the evidence base about putative mechanisms associated with metabolic pathways affected by EA.

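### The plan credits repeated-measures ANOVA of the secondary outcomes with a missing-data property it does not have, and this rule conflicts with the mixed-effect model named earlier in the protocol

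*Protocol*

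**What the plan says.** The protocol has two sections headed Statistical analysis.

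The first follows Secondary outcomes. Under Descriptive statistics it says: "A mixed-effect model will be used to compare change values before and after treatment for continuous variables". It fixes the covariates: "This analysis model divides the baseline scores as study covariates, accounting for grouping and central effects". The software is SPSS 26.0; no procedure within it is named.

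The second stands just before Risk. It says of the secondary outcomes: "Secondary outcome will be assessed following intention-to-treat principles". The method follows: "Repeated measures ANOVA will be conducted to assess changes in secondary outcomes throughout the study". It then claims of that method: "This model allows inclusion of missing data in an intention-to-treat analysis without imputations", giving last observation carried forward as an example of what is avoided. On covariates it says: "If necessary, analysis will be adjusted for baseline levels and potential confounding factors".

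The Secondary outcomes section lists an 11-point pain rating, a menstrual symptom scale, a Chinese medicine symptom score, and anxiety, depression and quality-of-life instruments. It describes the last three as "scales used to evaluate participants' mood and quality of life during treatment and follow-up". These are mostly scale scores taken more than once, so both sections cover them. Neither section says which one governs.

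**The concern.** Two things are wrong as written.

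First, the property claimed belongs to a different method. Classical repeated-measures ANOVA works on a complete row of visits per participant; one missing visit removes the whole participant. Using all available visits without imputation is a feature of a likelihood-based mixed model, and it is valid there if data are missing at random. An analyst who follows the text literally would report completers under an intention-to-treat label and believe that missing data had been dealt with.

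Second, the same continuous secondary outcomes fall under two rules that differ in model and covariates. Adjusting for baseline only where needed, with no stated trigger, leaves the choice open until the data are seen. Centre is in one rule and not named in the other, although the randomisation section generates a separate code series for each of the three centres.

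At stake are the analysis population, the precision and the pre-specification of the secondary results. Missing visits are foreseeable: participants may withdraw at any time, and outcomes run over 12 weeks of treatment and 12 weeks of follow-up.

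**Working it through.** **The two rules side by side**

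| | First section | Second section |
|---|---|---|
| Scope | continuous variables | secondary outcomes |
| Model | mixed-effect model on change values | repeated-measures ANOVA |
| Baseline | always a covariate | only if judged necessary |
| Centre | included | not named |
| Missing data | not stated | said to be included without imputation |

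For a continuous secondary scale score both columns apply, and they disagree on model, baseline and centre.

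**Does the method need complete visits?** A classical repeated-measures ANOVA routine (Python statsmodels) was run on simulated data for 20 participants at 3 visits with one observation deleted. It refused to fit and reported unbalanced data. The usual general linear model route in SPSS reaches the same end by deleting the participant.

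**How many participants would be lost?** The only document figure available is the total of 336 (168 per group). That total cannot be reproduced, because the protocol gives no effect size, standard deviation, power or dropout rate. The missingness rates and visit counts below are therefore assumptions, and baseline is taken as complete.

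*Plain dropout.* A share m leaves before the last visit, so completers = 336 × (1 − m):
- m = 5%: 336 × 0.95 = 319
- m = 10%: 336 × 0.90 = 302
- m = 20%: 336 × 0.80 = 269

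*Independent missingness m at each of k post-baseline visits.* Completers = 336 × (1 − m)^k:
- k = 3, m = 5%: 336 × 0.857 = 288
- k = 3, m = 10%: 336 × 0.729 = 245
- k = 6, m = 5%: 336 × 0.735 = 247
- k = 6, m = 10%: 336 × 0.531 = 179

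Three visits would be one per treated cycle. Six would add one per cycle over 12 weeks of follow-up (84 days / 28 = 3 cycles). Dropout in which people leave and do not return sits nearer the first set; scattered missed visits sit nearer the second.

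A likelihood-based mixed model for repeated measures would keep every participant with at least one post-baseline value. It still loses the information in the missing visits.

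**Is the completer estimate biased?** In one assumed missing-at-random scenario (4 visits, true difference −1, dropout in the sham arm depending on the previous score, 150 replicates, about 291 of 336 completers on average), completers gave −1.004 and the mixed model −1.002. One scenario does not show that completers are safe in general. It does show that bias cannot be taken as given.

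**The case against.** The strongest reply is that the authors meant a mixed model for repeated measures and used a loose name. The property stated is the right one for such a model, and no SPSS procedure is specified. On that reading only the name is wrong. But the text names ANOVA, the first section uses a different term for its mixed-effect model, and the conflict over baseline and centre would remain.

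Several limits do stand:

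- **Scope.** The ANOVA is assigned to secondary outcomes only. A reader might infer that the VAS comparison is undermined; the document does not support that, since the ANOVA and its missing-data claim are not attached to VAS.
- **Power.** A reader might assume 80% power at 336 (standardised difference 0.306) and infer a fall to 67% or 53% at 247 or 179 participants. The protocol states no power, effect size or visit count, and that calculation compares ANOVA with complete data. With 10% missing at a visit, about 302 contribute there even under a mixed model, and power is already about 76% before any borrowing across visits.
- **Bias.** A reader might infer that sham-arm dropout follows poor relief and tilts the result. The protocol says nothing on this; direction and size depend on the dropout mechanism.
- **The first section is not a full remedy.** It models change before and after treatment and does not mention repeated visits. With one change score per participant, it too would omit anyone without a post-treatment value.
- **Detail.** Covariance structure and estimation method belong in the SAP. The phrase on potential confounders does not strictly exclude centre.

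The second section also names feasibility rates (recruitment, completion, adherence, adverse events) as its primary outcome, against VAS under Primary outcomes. The conflict between the sections is therefore wider than the ANOVA sentence.

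**Conclusion.** The point holds for the continuous secondary outcomes. The missing-data statement is wrong for the method named, and the two sections set incompatible rules on model, baseline and centre. A later SAP could not comply with both, so this is more than detail left for that document.

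The certain consequences, if the text is followed literally and any visit is missed, are fewer participants, a completer set labelled intention-to-treat, and an open choice of model and covariates. The size is uncertain: 319 down to 179 of 336 participants retained across the assumptions shown. No figure for lost power and no direction of bias can be claimed from this protocol. Because the error does not reach the VAS analysis directly and wording cures it, it should be fixed but is not fatal to the design.

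**What to change.** In the second Statistical analysis section, delete the sentence assigning repeated-measures ANOVA, the missing-data claim attached to it, and the sentence making baseline adjustment conditional. In their place state one likelihood-based mixed model for repeated measures for the continuous secondary outcomes, and align the first section with it. The text should say that:

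- baseline value and centre are always included;
- all randomised participants with any post-baseline value are analysed;
- the analysis assumes data are missing at random.

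Covariance structure and estimation method can be left to the SAP. In the same edit, reconcile the feasibility rates named as primary outcome in the second section with the VAS under Primary outcomes; otherwise the two sections will still conflict.

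The cost is wording. No added participants, visits or data are needed, and SPSS, the package already named, can fit such a model.

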| **Sample Size:** Based on previousPDMM therapy intervention studies, n = 168 participants will be required per group (total n=336) for this study. | |

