**Intervention and exposure:**

Intervention group:

EA group

Hwato brand disposable acupuncture needles (size 0.30 ×40 mm), and SDZ-V （Suzhou Medical Device Co., Ltd）electroacupuncture apparatuses will be used. Participants in the EA group will be treated at the following acupoints: bilateral sanyinjiao (SP6), located in the medial calf, 3 cun (approximately 60 mm) above the tip of the medial malleolus (Fig 2A) behind the medial edge of the tibia; and guanyuan (CV4), located in the lower abdomen on the anterior midline, 3 cun below the umbilicus (Fig 2B). The acupoints will be routinely disinfected prior to treatment. Acupuncture needles will be inserted 0.8–1.5 cun (approximately 16–30 mm) into the skin. Needle insertion will follow an angle of 30–45° in an inferomedial direction for SP6.

Fig2. The point positioning diagram

The acupuncture needle will be inserted vertically into CV4. Following needle insertion, small, equal manipulations of twirling, lifting, and thrusting will be performed on all needles to reach de qi (a composite of sensations including soreness, numbness, distention, heaviness, and other sensations believed to be an essential component for acupuncture efficacy). After de qi is achieved, paired electrodes on the electric needle device will be connected to the needle handle on one side of SP6 and CV4. Electroacupuncture stimulation will last for 30 min a priori, with a continuous wave of 100 Hz, and current intensities of 1–5 mA (the skin around the acupoints shakes slightly, which participants can typically tolerate without pain). We will administer EA seven days before each menstrual cycle until menstruation is over. Each menstrual cycle equals one course of treatment. We will evaluate a total of three courses of treatment (i.e., three menstrual cycles) in the current study. A total of 21 treatments will be performed. During treatment, operators (i.e., operating personnel) will be separated from follow-up personnel. We will also control for other influencing factors to avoid information bias.

SA group

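### Repeated measures ANOVA does not have the missing-data property the protocol claims for it, and the protocol does not say whether it or the mixed-effect model governs the secondary outcomes

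*Protocol*

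**What the plan says.** The protocol has two sections headed Statistical analysis.

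The second, placed just before Risk, covers the secondary outcomes in three steps:
- Principle: "Secondary outcome will be assessed following intention-to-treat principles".
- Model: "Repeated measures ANOVA will be conducted to assess changes in secondary outcomes throughout the study".
- Missing data: "This model allows inclusion of missing data in an intention-to-treat analysis without imputations (e.g. last-observation-carried-forward".

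The subject of the third sentence can only be the ANOVA named in the second. The section gives no other method for missing data.

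The first, which follows Secondary outcomes, names the software, "We will perform statistical analyses using SPSS statistical software (version 26.0, IBM Corp., Armonk, NY, USA", and a different model: "A mixed-effect model will be used to compare change values before and after treatment for continuous variables". That model takes baseline as a covariate and accounts for group and centre. It is not limited to the primary outcome, so by its wording it also reaches the scored secondary scales.

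Neither section refers to the other.

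**The concern.** Classical repeated measures ANOVA works on one complete row of visits per participant. A participant with a missing visit has no complete row and is left out. Keeping incomplete participants without imputing is a property of a likelihood-based mixed model fitted to visit-level data, and the second section does not name that method.

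The issue is not that a missing-data plan is absent, which could be left to a statistical analysis plan. The protocol states a plan and attaches it to a method that cannot deliver it. A statistician who runs the named method would analyse completers and report the result as intention-to-treat.

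Missing visits are foreseeable. On treatment the protocol says "We will evaluate a total of three courses of treatment (i.e., three menstrual cycles) in the current study", and 12 weeks of follow-up come after that. Participants may withdraw at any time, and emergency unblinding turns a participant into a shedding case.

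**Working it through.** The disputed sentence contains no figure, so there is none to reproduce. The only design inputs in the text are the sample size, "n = 168 participants will be required per group (total n=336) for this study", and the significance level, "Statistical significance will be set at an alpha level of 0.05" (two-sided according to the first section). Everything else below is assumed.

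**1. Does the method have the property?** A standard repeated measures ANOVA routine (in Python) was given 20 subjects with 4 time points each and one cell removed. It refused the data as unbalanced. SPSS was not available for the check. That its usual repeated measures procedure deletes incomplete cases listwise is general software knowledge, not something the protocol states.

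**2. How many participants would be lost?** If each of m post-baseline visits is missed independently with probability q, the complete share is (1 − q)^m and the number kept is 336 × (1 − q)^m. For example, 0.98² = 0.960 and 336 × 0.960 = 323; 0.95⁶ = 0.735 and 336 × 0.735 = 247.

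| Visits m (assumed) | q = 2% | q = 5% | q = 10% |
|---|---|---|---|
| 2 | 323 | 303 | 272 |
| 4 | 310 | 274 | 220 |
| 6 | 298 | 247 | 179 |

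With 6 visits and q = 5%, 95% of the planned measurements exist, yet 336 − 247 = 89 women would be excluded.

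**3. What does that do to power?** The effect that 168 per arm detects with 90% power at two-sided 0.05 is (1.960 + 1.282) × √(2/168) = 0.354 SD. Power for that effect is Φ(0.354 × √(n/2) − 1.960):
- 5% of participants dropped, n = 159.6 per arm: 88.5%
- 10% dropped, n = 151.2: 86.8%
- 20% dropped, n = 134.4: 82.6%

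A mixed model also loses some information when visits are missing, so the shortfall from 90% is not all due to the choice of method.

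**4. Is there bias?** In a simulation of 1,500 trials with 168 per arm, the assumptions were SD 1.5, correlation 0.6, baseline plus 4 visits and a true last-visit difference of −1.20. From the second post-baseline visit onward, the log-odds of dropping out were −3.0 + slope × (last score − 4.5) in both arms.

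| Slope | Complete share, active / sham | Full data | Completers | Likelihood, all observed data |
|---|---|---|---|---|
| 0 (completely random) | 86% / 86% | −1.20 | −1.20 | −1.20 |
| 0.3 | 86% / 82% | −1.21 | −1.19 | −1.21 |
| 0.6 | 83% / 75% | −1.20 | −1.13 | −1.20 |
| 1.0 | 77% / 63% | −1.20 | −1.04 | −1.20 |

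Measured against the full-data estimate, completers are off by 0, about 0.01, 0.06 and 0.16, each time towards no effect. The likelihood estimate is essentially unbiased throughout, as it should be when dropout depends only on observed scores.

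A harsher assumption is that dropout depends on pain in the sham arm only. With SD 2, correlation 0.5 and a true difference of 1.0, two runs put completers at 0.71 and 0.63, against 1.00 and 0.99 for the likelihood model. The result depends on the assumed mean pain: in a similar model it ran from 0.83 at a mean of 3 to 0.37 at a mean of 6. With no true effect, completers gave −0.29 and −0.38 under sham-only dependence. They gave between −0.02 and 0.01 when the same mechanism acted in both arms.

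**The case against.** The strongest reply is that the protocol already contains a mixed-effect model for continuous variables. If that model were fitted by likelihood to all visits and governed the secondary scales, no complete-case analysis would arise. The second section's stated aim is to keep incomplete participants, so its ANOVA may simply be a misnamed mixed model. This stands in part. It means a reader cannot conclude that the trial's analysis will be complete-case, only that the method as named would be. It does not remove the problem. The first section speaks of before-after change and does not mention visit-level data or use of all available visits. A change score is itself missing when the later value is missing. The protocol does not say which section prevails.

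Three stronger readings are tempting and are not supported:
- A reader might infer that imputation is ruled out. The sentence claims a property of the model; it does not prohibit imputation.
- A reader might infer that the primary VAS comparison is affected, because the second section lists recruitment, completion, adherence and adverse-event rates as primary, which could push VAS down among the secondary outcomes. The Primary outcomes section and inclusion criterion 8 make VAS the primary endpoint, and the ANOVA is assigned to secondary outcomes. The mismatch over the primary outcome is a separate matter.
- A reader might infer that substantial bias is to be expected. It appears only under assumed pain-dependent dropout, most strongly when that dependence is confined to one arm.

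**Conclusion.** The point holds in this form: the missing-data property claimed for repeated measures ANOVA is wrong, and the two analysis sections name different models for the continuous secondary outcomes without an order of precedence. Under the ANOVA as named, participants with any missing visit would be lost from an analysis described as intention-to-treat.

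The size is illustrative. Roughly 323 down to 247 of 336 would be kept with 2 to 6 visits and 2% to 5% missed at each, if misses are independent. Bias ranges from none under completely random dropout to material when dropout follows recorded pain. Visit count, missingness rates, SD, correlation, effect and dropout mechanism are all assumptions. The likelihood model's advantage itself rests on data being missing at random.

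This should be fixed. It does not rank higher, because the ANOVA applies to secondary outcomes only and the protocol already names a mixed-effect model elsewhere.

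**What to change.** Reconcile the two Statistical analysis sections. In the second, replace repeated measures ANOVA with a likelihood-based linear mixed model for repeated measures. It should include all randomised participants by allocated arm and all their available visits, with baseline and centre handled as in the first section. State that the model is valid under missing at random; the sentence on missing data is then correct with that qualification. Add a line saying that this model governs the continuous secondary outcomes, so that the first section's before-after model cannot be read as a rival. The covariance structure and remaining detail can go in the statistical analysis plan.

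The cost is a few sentences of wording. SPSS, the software already named, offers the procedure, and no new data are needed. The protocol describes the study as preparing for recruitment, so on its own account the change can precede any outcome data. It does not resolve the separate disagreement over which outcome is primary.
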